### Assessment and analysis of outcome

The primary safety outcome of stage 1 is the proportion of participants with regimen discontinuation for safety reasons at the end of the first 8 weeks of treatment (regimen discontinuation is defined as greater than or equal to one drug permanent withdrawal from the assigned regimen). The safety outcomes measured in both stages include the AEs and SAEs assessment, the proportion of participants with grade 3 or higher AEs during the period of treatment.

The primary efficacy endpoint is the proportion of favorable outcomes at 78 weeks after the first dose for both stages. Besides, the secondary outcomes of stage 1 include liquid culture conversion rate at the 8 weeks of treatment, the proportion of participants with favorable outcomes at 104 weeks after the first dose, and incidence of acquired resistance during treatment and follow-up. The secondary outcomes of stage 2 include the percentage of participants with favorable outcomes at 104 weeks after the first dose, recurrence rate after treatment completion, proportion of sputum solid and liquid culture conversion at 8 weeks and at the end of the treatment, median time of sputum solid and liquid culture conversion, and rate of acquired resistance during treatment and follow-up.

For each participant, treatment outcomes includes favorable outcome, unfavorable outcome and not assessable outcome, as described in Table 3.

**Table 3 Tab3:** Definition of the favorable and unfavorable outcomes in ORIENT study

Outcome	Description
Favorable outcome	The outcome will be classified as favorable if not classified as unfavorable or not assessable and meets any one of the following criteria
	1) The sputum culture is negative for *M. tuberculosis* at the end of follow-up period 2) The sputum can be contaminated or no longer be produced at the end of follow-up period, without evidence of active pulmonary tuberculosis after a stable sputum culture conversion^a^ has been achieved
Unfavorable outcome	The outcome will be classified as unfavorable if:
	1) Sputum culture is positive for *M. tuberculosis* for two consecutive times after treatment; And the second strain is confirmed indistinguishable from the original isolate by the whole genome sequencing. If the whole genome sequencing result is not available, it defaults to the same strain
	2) The sputum culture at the last visit of follow-up is positive for *M. tuberculosis*
	3) Participants die during treatment (excluding force majeure factors such as homicide, traffic accidents or natural disasters); death associated with tuberculosis during follow-up (after completion of study treatment)
	4) Withdrawal from the trial or loss to follow-up during treatment (except pregnancy, accident, etc.)
	5) Participants stop the initial treatment, and restart different tuberculosis treatments
	6) Restart tuberculosis treatment after the end of expected treatment
	7) The treatment course exceeds the expected treatment length by more than 2 weeks regardless of any reason
	8) The treatment regimen is changed (including dosage or frequency of administration) except for pregnancy, exogenous reinfection, and rechallenge
Not assessable	The outcome will be classified as not assessable if not classified as unfavorable and meets any one of the following criteria: 1) Loss to follow-up (after completion of study treatment) with the last sputum culture being negative; 2) Sputum cannot be produced or is contaminated at the end of follow-up period, but stable culture conversion has not been achieved before and the last sputum culture is negative; 3) Alteration of treatment due to pregnancy; 4) Death unrelated to tuberculosis during follow-up (after completion of study treatment); 5) Death due to force majeure such as homicide, car accident or natural disaster during treatment; 6) Extension or change of tuberculosis treatment after the whole genome sequencing confirms exogenous reinfection

^a^Stable culture conversion is defined that the subject shows negative culture of *M. tuberculosis* in two consecutive samples (at least 2 weeks apart) for the first time, and subsequently no positive culture of *M. tuberculosis* or only one single positive (at least two consecutive bacterial cultures after the definition of the positive strain are negative, and no evidence of exogenous reinfection is found after sequencing of the positive strain) is shown

All subjects who have taken at least one dose of the treatment will be included in the safety analysis. The analysis for efficacy in this study will be conducted with modified intention-to-treat (mITT), assessable, and per-protocol populations with primary consideration for mITT results. For the primary outcome measurement in stage 2, the upper bound of the 95% confidence interval for the difference in favorable outcome between the control arm and the rifapentine arms must be less than 6.6% (the margin of non-inferiority) in the mITT populations for the rifapentine regimen to be declared non-inferior to the WHO standardized regimen.

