### Study regimens and comparator

The rifapentine regimens are composed of two periods of 17 to 26 weeks. The first phase is an 8-week intensive phase, including rifapentine (P), isoniazid (H), pyrazinamide (Z), and moxifloxacin (M) for daily use. This is followed by a 9-week continuation phase with the following agents every day: rifapentine, isoniazid, and moxifloxacin (8wHPZM/9wHPM) (The continuation phase should be extended to maximum of 18 weeks for patients who have lung cavitation at the end of 17 weeks treatment on chest radiography or positive sputum culture in liquid medium at the end of 8 weeks treatment (8wHPZM/18wHPM)). The control regimen is the WHO standardized regimen with two phases of treatment for 26 weeks. The first is an intensive phase using rifampicin, isoniazid, pyrazinamide, and ethambutol (E) every day for 8 weeks. This is followed by a continuation phase of 18 weeks with the following agents for daily use: rifampicin and isoniazid (8wHRZE/18wHR). Table 1 shows the doses and usage of each drug in the WHO standardized regimen and the short regimen with rifapentine.

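### On-treatment outcome rules span 26 weeks in control but 17 by default in the rifapentine arms, which favours the short arms in grade 3+ AEs and wherever not-assessable patients are dropped

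*Protocol article*

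**What the plan says.** **Treatment length** (Study regimens and comparator). For control: "The control regimen is the WHO standardized regimen with two phases of treatment for 26 weeks". For the rifapentine arms, after 8 intensive weeks: "This is followed by a 9-week continuation phase with the following agents every day", which makes 17 weeks. Some patients go on longer: "The continuation phase should be extended to maximum of 18 weeks for patients who have lung cavitation" on the week-17 radiograph, or who have a positive liquid culture at week 8. Their total is up to 26 weeks. The article does not say what share this will be.

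**Outcome classes** (Assessment and analysis of outcome, Table 3).
- Loss: unfavourable if "Withdrawal from the trial or loss to follow-up during treatment (except pregnancy, accident, etc"; not assessable if "Loss to follow-up (after completion of study treatment) with the last sputum culture being negative".
- Death: unfavourable if "Participants die during treatment (excluding force majeure factors such as homicide, traffic accidents or natural disasters" applies, or if it is a "death associated with tuberculosis during follow-up (after completion of study treatment". A death unrelated to TB after treatment is not assessable.

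**Safety** (same section). One named outcome in both stages is "the proportion of participants with grade 3 or higher AEs during the period of treatment".

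**Analysis sets** (same section). mITT is primary, with assessable and per-protocol sets beside it. Non-inferiority is declared on mITT with a margin of 6.6 points.

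**The concern.** The end of treatment is fixed by the assigned regimen and, within the rifapentine arms, by response. Using it as the boundary between outcome classes means that the same event on the same day can be classed differently by arm. Take a patient with a negative last culture who is lost at week 20. In control this is a failure. After a 17-week course it is not assessable. A non-TB death at week 20, not due to force majeure, splits in the same way.

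Wherever not-assessable patients leave the denominator, these events lower the control proportion only. In a non-inferiority trial that pushes toward the conclusion sought. The grade 3+ AE proportion has a similar fault: control is observed for nine more weeks than a 17-week patient, so equal toxicity per week looks like lower toxicity in the short arms. Rifapentine safety is the concern that motivates the trial, so this comparison will be read closely.

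The article uses a common clock from first dose elsewhere: 78 and 104 weeks for efficacy, and 8 weeks for the stage 1 safety endpoint. The items here are exceptions written into the stated definitions.

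**Working it through.** **1. The plan's own figures.** Inputs from Sample size assumptions: success 85.4% (control) and 84.5% (test), margin 6.6 points, power 80%.

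n = (z₁₋α + z₀.₈₀)² × [0.854×0.146 + 0.845×0.155] / (0.066 − 0.009)²

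- α = 0.025 one-sided: 618 per arm, as stated.
- α = 0.05 one-sided: 487 per arm, as stated.
- Inflation by 1/(1 − 0.24): 814 and 641 per arm, totals 2442 and 1282, as stated.

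**2. Window lengths.** 26 − 17 = 9 weeks. After treatment, to week 78: 78 − 17 = 61 weeks on the short course, 78 − 26 = 52 in control.

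**3. Shift when not-assessable patients are excluded.** Assume equal, constant loss in both arms, all with a negative last culture. Let L be total loss over 78 weeks and s the share of rifapentine patients treated for 17 weeks.

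q = L × (9/78) × s; shift ≈ 0.854 × q

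The factor 0.854 enters because only patients who would otherwise have been favourable change the control proportion. L = 12% borrows the plan's allowance for patients not assessed. The values of s and the even timing are assumptions.

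| L | s | q (points) | shift (points) |
|---|---|---|---|
| 12% | 50% | 0.69 | 0.59 |
| 12% | 80% | 1.11 | 0.95 |
| 12% | 100% | 1.38 | 1.18 |
| 4% | 50% | 0.23 | 0.20 |
| 4% | 100% | 0.46 | 0.39 |

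The 4% rows borrow the stage 1 loss rate. At the other extreme, if all 12% were lost within 26 weeks (9/26 in place of 9/78), the shift is 1.8 to 3.6 points for s from 50% to 100%.

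**4. One-sided error at a true difference equal to the margin** (85.4% against 78.8%), per comparison, in an analysis that excludes not-assessable patients.

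SE = √[(0.854×0.146 + 0.788×0.212)/618] = 0.0217

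error = Φ(shift/SE − 1.96)

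- L = 12%, s = 50% / 80% / 100%: 4.6% / 6.4% / 7.8%, against 2.5%.
- L = 4%, s = 50% to 100%: 3.1% to 3.8%.
- 487 per arm at one-sided 5%, L = 12%: 8.0% / 10.4% / 12.3%.

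**5. mITT.** If not-assessable patients stay in the denominator as not favourable, the week-20 patient is not favourable in either arm and the shift is 0. The article points both ways. A separate assessable set suggests that they stay in mITT. The sample-size allowance for 12% not assessed suggests that they are removed.

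**6. Grade 3+ AEs at equal constant hazard.** The control rates are illustrative; the article gives none.

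17-week rate = 1 − (1 − r)^(17/26)

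- r = 20%: 13.6% if all are on 17 weeks; 0.5 × 13.6% + 0.5 × 20% = 16.8% if half are extended.
- r = 10%: 6.7% and 8.3%.

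**The case against.** The decision rests on mITT. The endpoint is the proportion of favourable outcomes, and a separate assessable set is named, so the natural reading keeps not-assessable patients in mITT as not favourable. The shift there is then zero, and the error rates above belong to a supporting analysis. This stands, but the sample-size allowance points the other way and the article does not settle it.

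The second argument is that counting per regimen reflects the aim of the trial. A control patient lost at week 20 has not finished treatment and a 17-week patient has; less default and less toxic exposure are intended benefits. This also stands in part. It is a reason to keep the on-treatment AE figure, not a reason to have no common-window figure beside it. The stage 1 selection endpoint, at 8 weeks in every arm, is not affected.

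There is also an opposite effect: relapse and retreatment can be observed for 61 weeks after a short course and 52 after control. That works against the short arms, but it does not correct the different classing of the same loss.

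A reader might infer more than the text supports:
- That most rifapentine patients stop at 17 weeks. This is the default, but no share is given.
- That all deaths are counted unequally. TB deaths are unfavourable in both periods, and force majeure deaths on treatment are already not assessable. Only other non-TB deaths differ.
- That the per-protocol analysis is biased in the same way. The article does not define that set; if non-completers are left out, the control patient lost at week 20 drops out too.
- That the error reaches about 9%. That takes the full 1.38 points as the shift, without the control success factor, and puts every rifapentine patient on 17 weeks.

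**Conclusion.** The concern holds with limited reach. The unequal windows are in the text and their direction is clear. The grade 3+ AE proportion is affected for every patient on the 17-week course. The assessable analysis is affected, taking its name to mean that not-assessable patients are left out. The primary mITT analysis is affected only if such patients are excluded from it too.

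The size is a shift of about 0.6–1.2 points against a 6.6-point margin, with one-sided error of about 4.6–7.8% in place of 2.5% (618 per arm) in an analysis that excludes them. This rests on 12% loss spread evenly over 78 weeks and 50–100% of rifapentine patients on 17 weeks. The 12% is a stand-in, because Table 3 makes on-treatment loss unfavourable and not unassessed. Loss at 4% would give 0.2–0.4 points.

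The AE gap of 3.2 to 6.4 points (20% against 16.8% or 13.6%) assumes a constant hazard. It is smaller if events cluster early, and part of a lower on-treatment count is a real benefit of a shorter course.

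**What to change.** 1. **mITT.** State that not-assessable patients count as not favourable, and reconcile the 12% not-assessed allowance in Sample size assumptions with that rule.
2. **Assessable set.** Add a sensitivity analysis that classifies loss, withdrawal and non-TB death by one cut, week 26 from first dose, in every arm.
3. **Grade 3+ AEs.** Keep the on-treatment proportion. Beside it, report the proportion from first dose to one common week in all arms, ascertained at the first visit at or after that week.

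The cost is analysis wording. The 618 and 487 per arm do not change as long as the assumed success rates refer to the same outcome definition. The short arms will show slightly more unfavourable outcomes in the sensitivity analysis. Ascertainment there is sparser after week 17: post-treatment visits are 12 to 14 weeks apart (Duration of follow-up), so a 17-week patient's first may fall around weeks 29–31 (17 + 12 to 17 + 14). The detailed schedule is not shown, so the common week should be chosen with it in hand.

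### Table 3 of the primary endpoint is inconsistent: unfavorable items 5 to 7 override the table's own reinfection exemption, and its pregnancy exemption when treatment is replaced or over-runs by more than 2 weeks

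*Protocol article*

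**What the plan says.** All the rules are in Table 3 of the protocol article, under Assessment and analysis of outcome. The same section makes the proportion with a favorable outcome at 78 weeks the primary efficacy endpoint for both stages.

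- **Order of the categories.** Unfavorable comes first: "The outcome will be classified as not assessable if not classified as unfavorable and meets any one of the following criteria".
- **Unfavorable items that carry an exception.** Item 1 (two consecutive positive cultures after treatment) counts only if sequencing shows the original strain, with the same strain assumed when sequencing is unavailable. Item 4 exempts pregnancy: "Withdrawal from the trial or loss to follow-up during treatment (except pregnancy, accident, etc". Item 8 (changed regimen, dosage or frequency) exempts pregnancy, exogenous reinfection and rechallenge.
- **Unfavorable items without one.** Item 2: "The sputum culture at the last visit of follow-up is positive for" M. tuberculosis. Item 5: the initial treatment is stopped and a different one started. Item 6: "Restart tuberculosis treatment after the end of expected treatment". Item 7: "The treatment course exceeds the expected treatment length by more than 2 weeks regardless of any reason".
- **Not assessable items on the same events.** Item 3: "Alteration of treatment due to pregnancy". Item 6: "Extension or change of tuberculosis treatment after the whole genome sequencing confirms exogenous reinfection".

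**The concern.** Items 1 and 8 and Not assessable 6 show that the table does not mean to count a new infection as a failure of the regimen. Items 4 and 8 and Not assessable 3 show the same intention for pregnancy. Items 5, 6 and 7 have no matching exception, and because unfavorable is applied first, they decide the outcome wherever they overlap with a not-assessable item. Item 7 also rules out reading in an implied exception.

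Followed literally, the table codes as failures some events that it elsewhere sets aside. A programmer or adjudicator who follows the evident intention would code them differently. At stake are the primary endpoint and membership of the assessable population, which the article lists beside the mITT and per-protocol populations.

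**Working it through.** **Classification.** Each scenario was run through unfavorable items 4 to 8, then Not assessable 3 and 6, in the table's stated order.

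| Event | Exogenous reinfection (sequencing-confirmed) | Pregnancy |
|---|---|---|
| In-course change, length within 2 weeks of expected | Not assessable 6 (item 8 exempts) | Not assessable 3 (item 8 exempts) |
| Extension of at most 2 weeks | Not assessable 6 | Not assessable 3 |
| Extension of more than 2 weeks | **Unfavorable, item 7** | **Unfavorable, item 7** |
| Stopped, different treatment started | **Unfavorable, item 5** | **Unfavorable, item 5** |
| Treatment restarted after the expected end | **Unfavorable, item 6** | Unfavorable, item 6 |
| Withdrawal during treatment | not covered by Not assessable 6 | not unfavorable (item 4 exempts) |

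Three things follow.

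1. The extension part of Not assessable 6 survives only for over-runs of 2 weeks or less.
2. A participant whose post-treatment positive cultures escape item 1 because the strain is new becomes unfavorable under item 6 once re-treated. Item 6 thus undoes item 1's strain condition. Item 2 has no strain condition either, which is a softer tension with item 1.
3. For pregnancy, the direct conflict with Not assessable 3 and with the exemptions in items 4 and 8 is confined to items 5 and 7.

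**Size.** The article gives no rate for these events, so only an illustration is possible.

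Inputs from Sample size assumptions and the margin statement: favorable rates pC = 0.854 and pT = 0.845, margin 0.066, power 80%, α = 0.025 for three arms.

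The plan's figure first. The variance sum is 0.854×0.146 + 0.845×0.155 = 0.25566, and the distance to the margin is 0.066 − 0.009 = 0.057. Then n = (1.960 + 0.842)² × 0.25566 / 0.057² = 617.6, so 618 per arm. This matches the article, with α one-sided.

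Power = Φ(distance / SE − 1.960), with SE = √{[pC(1 − pC) + pT(1 − pT)] / n}. At n = 618, SE = 0.02034 and power is 80.0%.

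Let a share q of each arm be affected (assumed 1% to 3%), with 618 counted before any exclusion.

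- *Excluded as not assessable:* n = 618(1 − q), rates unchanged.
- *Coded as failures:* n = 618, both rates multiplied by (1 − q), distance = 0.066 − 0.009(1 − q).

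| q | n if excluded | Power, excluded | Rates if failed | Power, failed | Loss (points, unrounded inputs) |
|---|---|---|---|---|---|
| 1% | 611.8 | 79.6% | 84.55% / 83.66% | 78.4% | 1.3 |
| 2% | 605.6 | 79.2% | 83.69% / 82.81% | 76.8% | 2.4 |
| 3% | 599.5 | 78.8% | 82.84% / 81.97% | 75.3% | 3.5 |

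If the mITT analysis keeps not-assessable participants in the denominator as not favorable, the two codings give the same primary result and the loss is zero.

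**The case against.** The strongest reply is that the table works as written. Item 8 exempts both pregnancy and reinfection, item 4 exempts pregnancy, and the precedence clause yields one answer for every participant. Item 7 may be a deliberately conservative rule. A restart after the expected end is arguably neither an extension nor a change, so item 6 need not contradict Not assessable 6. Item 2 does not contradict it directly either.

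Much of this stands, and it rules out several stronger readings that a reader might infer:

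- **That Not assessable 3 and 6 can hardly be reached.** The classification table shows that in-course changes and short extensions still reach them.
- **That one participant receives two outcomes, or that staff who know the arm can choose.** The literal coding is deterministic, and the article does not say that site staff assign the outcome.
- **That power falls by 2 to 6 points.** Lowering both rates by 1 to 3 points and comparing with 80% gives 77.9%, 75.9% and 74.1%. That ignores the sample also lost when these participants are excluded.
- **That the rifapentine arms carry 17% more post-treatment time at risk.** The ratio (78 − 17)/(78 − 26) = 61/52 = 1.17 is an upper bound, because some rifapentine participants are treated for up to 26 weeks. It also bears on post-treatment items, not on item 7.

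What the reply does not answer is why reinfection is exempt in items 1 and 8 and Not assessable 6 but not in items 5 to 7. If item 7 is deliberate, the extension part of Not assessable 6 is almost empty. Nor is this a gap left by condensing a longer document: the table itemizes its exceptions, and its lines conflict.

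**Conclusion.** The inconsistency is real and sits in the primary endpoint definition. It is clearest for reinfection: item 7 cancels the extension part of Not assessable 6 beyond 2 weeks, item 5 overrides it for replacement treatment, and item 6 defeats the strain condition of item 1. For pregnancy it is limited to treatment that is stopped and replaced or over-runs by more than 2 weeks.

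The effect cannot be quantified from the article. The loss of 1.3 to 3.5 points of power rests on an assumed 1% to 3% of participants following an affected route, equally in both arms, and on not-assessable participants otherwise being excluded. The sample size inflation for participants who cannot be assessed (with the microbiological allowance, 618/0.76 = 813.2, giving 814) hints at exclusion but does not settle it. If the mITT analysis counts them as not favorable, only the assessable analysis is affected.

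**What to change.** Before outcomes are classified, reconcile items 5 to 7, and the missing strain condition in item 2, with items 1, 4 and 8 and Not assessable 3 and 6. Either of two routes would do:

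- carry the table's own exceptions for pregnancy and sequencing-confirmed reinfection into the items that lack them; or
- state explicitly which rule takes precedence for these events. If item 7 is meant to stand for any reason, Not assessable 3 and 6 should be reworded to match.

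Which route to take is for the trial team. The change concerns outcome classification only, not patient management. It costs an edit to Table 3 and to the outcome algorithm, and needs no new data.

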### Pharmacokinetic sampling

Sampling for pharmacokinetic analysis of anti-TB drugs is performed for all participants with rifapentine regimens in stage 1. Pharmacokinetic sampling is divided into intensive and sparse sampling, and 20 to 30 people in each rifapentine group perform intensive sampling and all other participants undergo sparse sampling.

An intensive sampling scheme includes two samplings. The first intensive sampling is at the first dose after randomization, and 4 ml venous blood is obtained at 0 h before administration and 0.5 h, 1 h, 2 h, 4 h, 6 h, 8 h, 12 h, 24 h, 48 h, 72 h, and 96 h after administration, respectively. The second intensive sampling will be permitted at any time between the 11th study drug dose and the week 8 visit, and blood samples, 4 ml each, is collected over a 96-h period at the same time as the first intensive sampling. Subjects do not take any anti-TB drugs during the intensive sampling period. For patients participating in intensive sampling, the first administration is not included in the course of treatment, meaning that the treatment period begins with completing the first sampling (the fourth day of the first sampling).

Patients participating in sparse sampling are sampled during routine follow-ups between week 2 and week 8 visits. The volume of venous blood collected at each follow-up for sparse sampling is approximately 4 ml, and the collection time will be recorded. Blood specimens will be shipped to the designated laboratory, in which concentrations of moxifloxacin, rifapentine, and metabolites of rifapentine are measured.

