**Methods:**

ORIENT is a multicenter, randomized controlled, open-label, phase II/III, non-inferiority trial involving DS-TB patients to evaluate the safety and efficacy of short-term regimens compared with the standardized six-month treatment regimen. In stage 1, corresponding to a phase II trial, a total of 400 patients are randomly divided into four arms, stratified by site and the presence of lung cavitation. Investigational arms include 3 short-term regimens with rifapentine 10 mg/kg, 15 mg/kg, and 20 mg/kg, while the control arm uses the standardized six-month treatment regimen. A combination of rifapentine, isoniazid, pyrazinamide, and moxifloxacin is administered for 17 or 26 weeks in rifapentine arms, while a 26-week regimen containing rifampicin, isoniazid, pyrazinamide, and ethambutol is applied in the control arm. After the safety and preliminary effectiveness analysis of patients in stage 1, the control arm and the investigational arm meeting the conditions will enter into stage 2, which is equivalent to a phase III trial and will be expanded to recruit DS-TB patients. If all investigational arms do not meet the safety conditions, stage 2 will be canceled. In stage 1, the primary safety endpoint is permanent regimen discontinuation at 8 weeks after the first dose. The primary efficacy endpoint is the proportion of favorable outcomes at 78 weeks after the first dose for both two stages.

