### Duration of follow-up

After screening and baseline assessment, follow-up visits will be conducted every 3 days to 2 weeks in the 8-week intensive phase, every 4 to 5 weeks until the end of treatment, every 12 to 14 weeks at the period of post-treatment until 78 weeks after treatment initiation, and the last follow-up visit is 104 weeks after treatment initiation. All patients undergo intensive monitoring of liver function and blood routine, especially for the first two weeks after the first dose. During the follow-up, physical examination, clinical assessment, weight measurement, sputum smear, sputum culture, blood routine, liver function, renal function, electrocardiogram, ophthalmologic examination, and other adjuvant examinations will be done according to schedule (the Additional file). Study enrollment began in November 2022.

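### The safety outcomes run from two different starting points, and for intensive-PK patients in the rifapentine arms these lie about 4 days apart

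*Protocol article*

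**What the plan says.** All references are to the protocol article.

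- **Abstract, Methods:** "the primary safety endpoint is permanent regimen discontinuation at 8 weeks after the first dose". The section Sample size assumptions uses the same first-dose origin when it sets the expected discontinuation rate at 20%.
- **Assessment and analysis of outcome:** the same endpoint becomes "regimen discontinuation for safety reasons at the end of the first 8 weeks of treatment". The safety outcomes of both stages include "the proportion of participants with grade 3 or higher AEs during the period of treatment".
- **Pharmacokinetic sampling:** "Sampling for pharmacokinetic analysis of anti-TB drugs is performed for all participants with rifapentine regimens in stage 1", of whom "20 to 30 people in each rifapentine group perform intensive sampling". For this subgroup "The first intensive sampling is at the first dose after randomization", samples run to 96 hours, and "the first administration is not included in the course of treatment, meaning that the treatment period begins with completing the first sampling".

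For controls, and for rifapentine patients with sparse sampling, no rule separates the first dose from the start of treatment, so the two origins coincide.

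**The concern.** In most trials, 8 weeks after the first dose and the first 8 weeks of treatment are the same interval. Here the pharmacokinetic section makes them different for one subgroup, and that subgroup exists only in the investigational arms. The article does not say which origin governs the safety outcomes.

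Two things follow from a literal reading. First, the days after first exposure to the study dose of rifapentine lie before the treatment period in intensive-PK patients, so a severe event in those days is missing from the grade 3 or higher outcome. It would be counted in a control, or in a sparse-sampling patient of the same arm. Second, the date on which week-8 discontinuation is read depends on the section followed. That endpoint feeds the stage 1 decision in an open-label trial, so the reading date should not be open to choice once the data are known.

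**Working it through.** **The plan's own figure.** The go rule requires the one-sided 90% upper bound for discontinuation to be below 30%, and the assumed rate is 20%. An exact binomial test of 30% against 20% with α = 0.10 and n = 96 passes an arm with at most 22 discontinuations: P(X ≤ 22 | 0.30) = 0.078 and P(X ≤ 22 | 0.20) = 0.802. With 4% loss, 96 / 0.96 = 100 per arm. The stated 96 and 100 reproduce, and nothing below changes them.

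**Size of the shift.** 96 h / 24 = 4 days. Against an 8-week window of 56 days, 4 / 56 = 7.1%. Counted from the first dose, the week-8 reading is at day 56 on the first-dose clock and at day 4 + 56 = 60 on the treatment clock.

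**Who is affected.** 20 to 30 of 100 patients in each rifapentine arm (20% to 30%), so 3 × 20 = 60 to 3 × 30 = 90 in all, and 0 of 100 controls.

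**What each clock does to an event in an intensive-PK patient** (days from the first dose, events dated by onset):

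| Event | First-dose clock | Treatment clock |
|---|---|---|
| Grade 3+ adverse event, days 0–4 | counted | not counted |
| Permanent drug withdrawal, days 0–4 | counted at day 56 | counted at day 60 |
| Permanent drug withdrawal, days 56–60 | not counted | counted |
| Drug-related serious event, liver failure or death, days 0–4, for the arm-stopping rules | counted | counted (no window stated) |

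In a control patient the two columns are identical: a grade 3 or higher event on days 0–4 counts, and a withdrawal after day 56 does not.

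The second row follows from the definition. Discontinuation is the permanent withdrawal of at least one drug, read at a time point, and anyone with one dose is in the safety analysis. A drug permanently withdrawn on day 2 is still withdrawn at day 56 and at day 60.

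**Possible size for grade 3+ events.** The documents give no event rate after a single dose. Assuming 1% to 10% of intensive-PK patients have a grade 3 or higher event in those 4 days, the number left out per arm is between 20 × 0.01 = 0.2 and 30 × 0.10 = 3.0, or 0.2 to 3 percentage points of 100 patients. The upper end is a deliberately wide assumption.

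**The case against.** The case for leaving this alone is fairly strong. The pharmacokinetic section speaks of the course of treatment, which most naturally concerns how long treatment lasts, and says nothing about how safety is counted. The Abstract and the sample size section both use the first dose. The safety population needs only one dose. Laboratory monitoring is also tied to that dose ("especially for the first two weeks after the first dose"), all adverse events and withdrawals are recorded, and serious events go to the safety committee within 24 hours. Exact windows are often left to the full protocol.

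Most of this stands, and it limits the finding. It does not remove it. The same sentence that excludes the PK dose also states when the treatment period begins, and the outcome section uses that period as the window for grade 3 or higher events. The first-dose wording elsewhere concerns discontinuation only and does not settle that outcome. Being in the safety population fixes the denominator, not the event window. This is a conflict between statements that the article does make.

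A reader might go further and infer that early withdrawals drop out of the primary safety endpoint, so that a borderline rifapentine arm is more likely to reach stage 2. The documents do not support that. Withdrawal is a permanent state that is still present at week 8 on either clock. The only withdrawals on which the clocks differ are those at about days 56 to 60, and there the treatment clock counts more of them. Nor does a gap between rifapentine arms and control enter the go rule, which compares each arm with a fixed 30% limit.

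**Conclusion.** The finding holds in a narrow form: time zero for the safety outcomes is inconsistent, and the inconsistency affects 20% to 30% of each stage 1 rifapentine arm and no controls. Its clearest consequence is that grade 3 or higher events in the roughly 4 days after the first dose are, on the literal wording, omitted in intensive-PK patients only. Its second consequence is a 4-day ambiguity in the week-8 discontinuation reading for the same patients.

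The impact is probably small. No shift in the go/no-go probability from lost early withdrawals is shown, and the arm-stopping rules and the reporting of serious events are untouched. The conclusion assumes that treatment starts at the end of the 96-hour sampling, that events are dated by onset, and that the outcome section means the treatment period as the pharmacokinetic section defines it.

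**What to change.** Make the Abstract, Sample size assumptions, Assessment and analysis of outcome, and Pharmacokinetic sampling agree on three points:

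1. All safety outcomes (discontinuation, adverse events, grade 3 or higher events, serious events, deaths) are counted from the first dose of any study drug, including the PK dose.
2. The 8-week reading uses one stated time origin in all arms, fixed before the stage 1 decision. The first dose, already used in two of the sections, gives every patient the same 56-day window.
3. The exclusion of the PK dose applies only to counting the length of the course.

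The cost is a few sentences. The events are already recorded, so no new data are needed, and the sample size does not change. The downside is that grade 3 or higher rates in the rifapentine arms may come out slightly higher than under the literal wording.
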